#### **2.2.2 Secondary Objectives**

##### **Process Measures:**

1. To assess the effect of the CDSS on the underdiagnosis of CKD, as measured by the rate of appropriate ICD-coded documentation in patient records.
2. To examine the change in the utilization rates of renoprotective medications (RAASi and sodium-dependent glucose transporters 2 inhibitor [SGLT2i]) among CKD patients.
3. To evaluate the impact of the CDSS on the screening rate for CKD (SCr and/or urine protein testing) among patients at high risk for CKD.
4. To determine the effect of the CDSS on the referral rate of CKD patients who meet guideline-based criteria for nephrology consultation.

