#### 3.1 Research Subjects

##### 3.1.1 Study Population

The study population comprise adult patients managed across 30 community health centers in Xicheng District, Beijing (**Table 1**). To ensure sufficient data for follow-up, patients were selected from all visits to these centers during a one-year screening period (March, 10, 2022 – March, 10, 2023), with the inclusion criterion of having at least two visits during this period. The study is primarily focused on CKD patients, while analysis will include a cohort of high-risk population for developing CKD. ICD codes for defining diseases in study population inclusion/exclusion criteria are summarized in **Table 2**.

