### 3.2.1 CDSS

The CDSS will be developed using a Plan-Do-Check-Act framework and will be integrated into the existing EHR system. In the Plan phase, semi-structured interviews with PCPs will be conducted to identify user needs. The Do phase will involve a multidisciplinary team (including nephrologists, technical experts, and PCP representatives) in designing an initial prototype. A pilot study at an independent primary care center will then be conducted as the Check phase, during which the system will be iteratively refined. Finally, the Act phase will consist of evaluating the system's effectiveness and implementation feasibility through the main clinical trial described above. The CDSS is designed to provide non-intrusive, real-time clinical decision support during patient encounters. The key functionalities deployed in the intervention arm include:

1. Automated case identification & risk stratification: The system automatically identifies patients with or at risk of CKD through structured diagnostic codes and laboratory data.

2. Renal referral for patients without prior diagnosis of CKD

- (1) Rapid decline in renal function meeting the AKD criteria (**Table 3**).

- (2) Presence of refractory hypertension: defined as blood pressure (BP) >140/90 mmHg while prescribed  $\geq 3$  antihypertensive medications, or being prescribed  $\geq 4$  classes of antihypertensive medications.

- (3) Persistently proteinuria, hematuria or eGFR <60 mL/min/1.73m^2 (two consecutive abnormal results obtained  $\geq 90$  days apart)

3. Automated CKD staging (stages 1-5)

4. Structured management protocols for diagnosed CKD patients:

- (1) Stage-specific monitoring of renal function (e.g., eGFR, UACR every 3 month).

- (2) Complication management alerts for identification, evaluation and management targets based on thresholds defined as follows: hypertension (BP >130/80 with proteinuria or >140/90 without), CKD-mineral and bone disorder (CKD-MBD) (corrected Ca2+ <2.2 mmol/L; PO4 >1.61 mmol/L), hyperkalemia (K+ >5.5 mmol/L), metabolic acidosis (pH <7.25 or HCO3 <22 mmol/L), anemia (Hb <120 g/L [Male] / <110 g/L [Female]), and dyslipidemia (LDL-C >1.8 mmol/L).

5. Renal referral for CKD patients presenting with following indications:

- (1) Advanced CKD (stage 4-5)

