### **3.3.2 Secondary Outcomes**

- 
1. Changes in CKD diagnosis rate: the difference in the proportion of CKD patients with an ICD-code for CKD documentation between the follow-up and baseline periods.
  2. Changes in utilization of renoprotective medications: the difference in prescription rates of RAASi and SGLT2i among CKD patients between the follow-up and baseline periods, reported separately.
  3. Changes in screening rate for CKD: the difference in the proportion of patients at high risk for CKD who complete SCr and/or urine protein testing between the follow-up and baseline periods.
  4. Changes in renal referral rate: the difference in the proportion of CKD patients meeting criteria for nephrologist consultation referral who are actually referred.
  5. Changes in blood pressure control rate: the difference in proportion of CKD patients achieving a target of <130/80 mmHg, based on available tests.
  6. Changes in glycemic control rate: the difference in the proportion of CKD patients achieving a HbA1c <7%, based on available tests.
  7. Changes in lipid control rate: the difference in the proportion of CKD patients achieving a LDL-C <2.6 mmol/L, based on available tests.
  8. Cost-effectiveness of the CKD-CDSS: economic evaluation of the community-based CKD screening and management program.
  9. CDSS implementation process: process evaluation using the RE-AIM framework (**Table 5**) to understand the implementation of this complex intervention. This evaluation examines the factors influencing outcomes across five dimensions—Reach, Effectiveness, Adoption, Implementation, and Maintenance—at both the individual and organizational levels. An initial phase, structured questionnaires for community institutions and physicians (**Table 6**) will be used to inform the timely optimization of the CDSS and its implementation strategy.

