## **4. Research Quality Control**

As a pragmatic clinical trial, this study will focus its quality control efforts on two key areas: the implementation of the intervention and the management of study data. Following randomization, PCPs at all participating centers will receive standardized training on the trial procedures. Those in the intervention group will receive additional, comprehensive training on the use of the CDSS. In contrast, PCPs in the control group will not be introduced to the CDSS and will only receive training pertinent to routine patient management. This will ensure a consistent understanding of the processes among all sites. Throughout the trial, centers will be required to adhere strictly to the protocol specifications regarding randomization, allocation concealment, and participant eligibility. To maintain the quality of CDSS implementation in real-world settings, a three-tier management system will be established. This system will enable weekly feedback, evaluation, and verification of CDSS-related clinical quality indicators at each community site, allowing for timely identification and continuous improvement of any operational issues.

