|                        | Beijing          | N20.003, N20.201, N20.901, N20.101, N20.000y003, N20.005, N20.902                                                                                                                                                                                                                                                                                                                                                                                                                                                                                                                                                                          |
| CKD                    | WHO              | N18.916, N18.917, N18.915, N18.914, N18.918                                                                                                                                                                                                                                                                                                                                                                                                                                                                                                                                                                                                |
|                        | China            | N18.803, N18.400, N18.200, N18.804, N18.500, N18.300, N18.801, N18.802, N18.001, N18.100                                                                                                                                                                                                                                                                                                                                                                                                                                                                                                                                                   |

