|                        | Beijing          | N18.916, N18.917, N18.915, N18.914, N18.918                                                                                                                                                                                                                                                                                                                                                                                                                                                                                                                                                                                                |
| Pregnancy              | WHO              | O10.2, O26.8, O23.2, O22.1, O30.9, O15.2, O24, O12.0, O26.6, O15.1, O22, O33.0, O26.9, O15, O33.4, O22.3, O34.1, O12.2, O34.2, O14.2, O13, O23.0, O24.2, O23.5, O21.0, O12.1, O20.8, O26.0, O32.4, O22.0, O14.9, O34.8, O22.9, O34.3, O20.0, O30.0, O30.8, P08.0, O26.5, O22.2, O30.1, O33.5, O21.1, O25, O24.4, O22.4,                                                                                                                                                                                                                                                                                                                    |

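### Table 2, the protocol's only CKD code list, omits N18, N18.9 and N18.900: unstaged CKD is missed at eligibility and, if the list also scores the diagnosis-rate outcome, recoding could count as new diagnosis

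*Protocol*

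**What the plan says.** Section 3.1.1 gives Table 2 its role: "ICD codes for defining diseases in study population inclusion/exclusion criteria are summarized in" that table. The CKD entry has three rows. The China row is "N18.803, N18.400, N18.200, N18.804, N18.500, N18.300, N18.801, N18.802, N18.001, N18.100". The Beijing row is "N18.916, N18.917, N18.915, N18.914, N18.918", and the WHO row holds the same five codes in the same order. No code has a label.

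Table 2 matters for eligibility through criterion 2(3) of section 3.1.2.1, which admits a patient with a CKD code plus one qualifying eGFR or proteinuria result. Criteria 2(1) and 2(2) need no code but require two abnormal results at least 90 days apart. The high-risk cohort in section 3.1.3.1 requires that no CKD diagnosis is established.

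Secondary outcome 1 in section 3.3.2 is "the difference in the proportion of CKD patients with an ICD-code for CKD documentation between the follow-up and baseline periods". It cites no code list. The matching objective in section 2.2.2 concerns underdiagnosis, "as measured by the rate of appropriate ICD-coded documentation in patient records".

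Section 3.2.1 introduces the system with "The key functionalities deployed in the intervention arm include", and its third item is "Automated CKD staging (stages 1-5" in number. Section 4 adds that "PCPs in the control group will not be introduced to the CDSS".

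**The concern.** A code list that leaves out the general CKD code treats a patient whose record says only CKD, without a stage, as having no CKD code. This has two possible consequences.

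The first is for cohort assignment. Such a patient can be lost to the CKD cohort and counted among those at high risk of CKD. Each cohort carries one of the two main hospitalization outcomes, so the make-up of both is affected.

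The second is conditional. If the list also forms the numerator of secondary outcome 1, the outcome mixes two things: whether CKD was recorded, and whether a stage was attached to the record. Only the first is underdiagnosis. The CDSS supplies a stage in one arm, so the second component could move differently between arms with no change in how many patients are recognised as having CKD.

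**Working it through.** The protocol states no figure to reproduce here. The check is of list membership, followed by an illustration.

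**1. What the CKD rows contain.** WHO 5 + China 10 + Beijing 5 = 20 entries. The WHO row repeats the Beijing row, so 20 − 5 = 15 distinct codes: N18.001; N18.100, .200, .300, .400 and .500; N18.801 to N18.804; N18.914 to N18.918. N18, N18.9 and N18.900 are all absent.

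**2. How the other rows of Table 2 are built.**
- Type 2 diabetes: parent code E11 (WHO) and E11.900 (China).
- Hypertension: I11.900, I12.900, I13.900 and I15.900 (China).
- Cardiovascular disease: I21.900, I25.900 and I50.900, among others (China).
- Obesity: E66.9 (WHO) and E66.900 (China).
- Kidney stone: N20.900 (China).
- Acute kidney injury: no plain .900 code, but the parent N17 is in the WHO row.
- CKD: neither a parent code nor a residual code.

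The CKD entry is therefore out of pattern within the table itself. The WHO row elsewhere mostly uses short codes. Five local-style codes identical to the Beijing row suggest a copying error there, but the China row lacks N18.900 independently.

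**3. Effect on eligibility.** Take a hypertensive adult with N18.900 on record and one eGFR below 60. Criteria 2(1) and 2(2) fail because there is only one result. Criterion 2(3) fails because the code is not listed. By the same list no CKD diagnosis is established, and hypertension is a listed risk factor, so the patient can enter the high-risk cohort. Entry uses screening-period records (10 March 2022 to 10 March 2023), so this should not differ by arm.

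**4. Effect on secondary outcome 1, if Table 2 is its list.** Let u be the share of CKD patients whose only CKD code at baseline is unstaged and unlisted. Let s_int and s_ctl be the shares of those patients who have a listed code by follow-up in each arm, with no true change in recognition.

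- Understatement of baseline documentation = u.
- Spurious difference between arms in change = u × (s_int − s_ctl).

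The documents give none of these three quantities. The values below are assumptions that show scale only.

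| u | s_int | s_ctl | Spurious gain (points) |
|---|---|---|---|
| 2% | 25% | 0 | 0.02 × 0.25 = 0.5 |
| 5% | 50% | 0 | 0.05 × 0.50 = 2.5 |
| 20% | 100% | 0 | 0.20 × 1.00 = 20 |
| 2% | 25% | 10% | 0.02 × 0.15 = 0.3 |
| 20% | 100% | 10% | 0.20 × 0.90 = 18 |

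The artefact is 0 if u = 0 or if s_int = s_ctl. It is also exactly 0, whatever u and s are, once unstaged codes count in the numerator.

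**The case against.** The strongest reply is that Table 2 is an eligibility list. Section 3.1.1 says so, and secondary outcome 1 cites no table. Read literally, that outcome accepts any CKD code, which is the scoring recommended here, and a statistical analysis plan not at hand may name the numerator codes. This stands: using Table 2 for the outcome is an inference, drawn because no other CKD list exists in the protocol.

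Second, the codes are unlabelled. N18.914 to N18.918 fall under N18.9, and N18.001 and N18.801 to N18.804 have no stated meaning, so an unstaged code may be present under another number. This also stands, and is why the point is put as three missing codes and not as the absence of every unstaged code.

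Third, the objective speaks of appropriate coding, so requiring a stage could be deliberate. If so, the outcome definition should say it, because it then measures more than underdiagnosis.

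A reader might go further and infer that the diagnosis-rate comparison is biased towards the CDSS and likely to reach significance with no true effect. The documents do not support that. Section 3.2.1 does not say that staging selects or writes an ICD code. Nothing shows how often unstaged codes are used. Section 3.2.2 trains both arms on monitoring by stage, which would narrow any gap. A false-positive rate would rest on coding shares with no source, and on an intraclass correlation set for hospitalization, not for coding.

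**Conclusion.** The omission is a fact of the document: no CKD row contains N18, N18.9 or N18.900, and the WHO row duplicates the Beijing row. Given the standard meaning of N18.9, it weakens the code-based inclusion route and can misplace patients between the two cohorts, equally in both arms. The number affected is unknown; patients with two qualifying results at least 90 days apart still enter the CKD cohort without a code.

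For secondary outcome 1 the finding is a conditional risk. It needs Table 2 to be the numerator list, unstaged codes to be in use, and recoding to differ by arm. If all three hold with more recoding in the intervention arm, baseline documentation is understated and the CDSS effect on diagnosis overstated, by an amount the documents cannot fix and that may be zero. The outcome is secondary; an artefact in scoring it would not carry over to the hospitalization outcomes. The point merits correction because the remedy is simple and removes the recoding artefact entirely.

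**What to change.** 1. Replace the WHO row of the CKD entry with the intended WHO codes.
2. Tabulate every N18 code found in the EHR, blind to arm, with its label. Then add the unspecified-stage CKD codes (WHO, national and local equivalents) to Table 2.
3. State in section 3.3.2 which codes form the numerator of secondary outcome 1, and define it as any CKD code, staged or unstaged, in both arms and both periods.
4. Report the proportion with a stage-specific code as a separate measure.

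The cost is one code-list edit and one extra table, with no new data collection. Some patients may move from the high-risk to the CKD cohort, baseline documentation may be higher, and the apparent effect of the CDSS on diagnosis may be smaller.

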### **3.1.2.2 Exclusion Criteria**

1. Pregnancy: Patients with pregnancy/perinatal ICD diagnosis codes in EHR.

2. Malignancy

3. End-stage kidney disease: maintenance kidney replacement or kidney transplantation by ICD codes, or  $\text{eGFR} < 15 \text{ mL/min/1.73m}^2$

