- (2) With any of the following complications: rapid eGFR decline meeting AKD criteria; persistent hematuria ( $\geq 20$  RBCs/HPF,  $\geq 80$  RBCs/ $\mu$ L, or occult blood  $\geq 2+$ ) on consecutive tests; refractory hypertension; hypoproteinemia (serum albumin <35g/L); CKD-MBD; severe anemia (Hb <100 g/L); significant proteinuria (UACR  $\geq 300$  mg/g

---

or UTP  $\geq 1.0$  g/day, or  $\geq 0.5$  g/day in diabetics); or persistent hyperkalemia ( $K^+ > 5.5$  mmol/L after initial treatment).

6. Treatment recommendations for CKD patients:

(1) SGLT2is are recommend as first-line treatment for patients with T2DM and an eGFR  $\geq 30$  mL/min/1.73 m^2.

(2) GLP-1 RAs are introduced for patients with T2DM and suboptimal glycemic control on metformin and SGLT2i, with eGFR  $\geq 15$  mL/min/1.73 m^2.

(3) RAASi are recommended for patients with proteinuria and/or hypertension, contingent upon the following criteria: eGFR  $\geq 30$  mL/min/1.73 m^2 (within the past 6 months), serum  $K^+ < 5.5$  mmol/L (within the past 6 months), and absence of bilateral renal artery stenosis.

(4) Dosing for all relevant medications should be adjusted according to renal function, as specified in **Table 4**.

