### **3.4.6 Informed Consent**

The study received ethical approval from the Peking University First Hospital (2022 Study 489) and the Xicheng District Health Commission (2021 Study 104). The ethics committee granted a waiver for individual patient informed consent, as the intervention was implemented at center level, posed minimal risk by adhering to guideline-based care, and did not alter routine care. This waiver was granted on the condition that we obtained prior administrative approval from all involved community health authorities.

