| Field search for AKI/AKD            | "acute renal failure", "acute kidney injury", "acute kidney disease", "acute renal failure"                                                                                                                                                                                                                                                                                                                                                                                                                                                                                                                                                                                                                                                                                                                                                                                                                              |

468 AKI, acute kidney injury; AKD, acute kidney disease; SCr, serum creatinine; eGFR,  
 469 estimated glomerular filtration rate.

470 **Table 4. Safety reminder for hypoglycemic drugs.**

| Drug Class                       | Common medications | Medication Reminders from Chinese Diabetic Nephrology Clinical Prevention and Treatment Guidelines                                                                                                                                                                                                                                                                                                                                                                                                 | Medication reminders                                                  |
|----------------------------------|--------------------|----------------------------------------------------------------------------------------------------------------------------------------------------------------------------------------------------------------------------------------------------------------------------------------------------------------------------------------------------------------------------------------------------------------------------------------------------------------------------------------------------|-----------------------------------------------------------------------|

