| Meglitinides                     | Nateglinide        | ○ eGFR <15: use with caution                                                                                                                                                                                                                                                                                                                                                                                                                                                                       | eGFR < 15: dose reduction                                             |
|                                  | Repaglinide        | ○ eGFR < 30, kidney transplantation and dialysis: reduction.                                                                                                                                                                                                                                                                                                                                                                                                                                       | eGFR < 30: dose reduction                                             |
| $\alpha$ -glucosidase inhibitors | Acarbose           | ○ eGFR < 25: contraindication                                                                                                                                                                                                                                                                                                                                                                                                                                                                      | eGFR <25: dose reduction                                              |
|                                  | Voglibose          | ○ eGFR < 30: use with caution                                                                                                                                                                                                                                                                                                                                                                                                                                                                      | eGFR <30: dose reduction                                              |

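### In Table 4 the acarbose reminder at eGFR below 25 is weaker than the contraindication the table attributes to its cited guideline, and no reason is given

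*Protocol*

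**What the plan says.** Section 3.2.1 (CDSS), item 6(4), makes Table 4 the dosing specification for CKD patients: "Dosing for all relevant medications should be adjusted according to renal function, as specified in" Table 4. It does not say which column of the table governs.

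Table 4 has two columns of advice for each glucose-lowering drug. One is headed "Medication Reminders from Chinese Diabetic Nephrology Clinical Prevention and Treatment Guidelines". The other is headed simply as medication reminders. In the acarbose row the guideline column reads "eGFR < 25: contraindication" and the reminder column reads "eGFR <25: dose reduction". The notes under the table only expand abbreviations.

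Three other places set the context:

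- Section 3.1.2.2 excludes "End-stage kidney disease: maintenance kidney replacement or kidney transplantation by ICD codes", and also eGFR below 15. Nothing else in the criteria removes patients for low eGFR.
- Section 3.4.6 records that individual consent was waived, one ground being that the intervention "posed minimal risk by adhering to guideline-based care".
- Section 4 states that "PCPs in the control group will not be introduced to the CDSS", so only intervention centres see the reminder.

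**The concern.** A reader who takes the reminder column as the adopted rule finds the CDSS advising a smaller dose of a drug that, by the table's own account, the cited guideline says not to use at that level of kidney function. A departure from a guideline can be legitimate, but here it goes in the less cautious direction, at an identical threshold, without explanation, in a table titled as a safety reminder.

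What is at stake is the content of the intervention and not its statistical evaluation. The text is delivered in one arm only, to patients who have not individually consented, under a protocol that describes the intervention as guideline-based. If the reminder is a slip, it should not stay in the rule table. If it is deliberate, the reason should be on record.

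**Working it through.** The plan states no figure to reproduce and no formula applies. The check has three parts.

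**1. Is the row intact?** Both acarbose cells are present and complete, with the same cut-off of 25. The difference is not a product of a broken table.

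**2. Is acarbose different from the other rows?** The two columns differ for several drugs, so a difference alone proves nothing; its direction matters. These are the readable rows in which the guideline column states a contraindication:

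| Drug | Guideline column: contraindicated | Reminder column | Direction |
|---|---|---|---|
| Metformin | below 45 | contraindicated below 45 | unchanged |
| Glyburide | below 30 | contraindicated below 60 | stricter |
| Gliquidone | below 15 | contraindicated below 30 | stricter |
| Pioglitazone | severe dysfunction, no number given | contraindicated below 30 | kept, with a number added |
| Empagliflozin | below 45 | contraindicated below 45 | unchanged |
| Acarbose | below 25 | reduce dose below 25 | **relaxed** |

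Five of the six rows keep or tighten the contraindication and one relaxes it. Glimepiride, gliclazide and glipizide are left out because their guideline cell appears to be merged with glyburide's and cannot be read with certainty.

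**3. Who falls in the range?** Patients below 15 are excluded at entry and the two acarbose cells disagree below 25. The affected range among eligible patients at entry is therefore eGFR from 15 up to, but not including, 25. The protocol does not say how many such patients there are or how many take acarbose.

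**Side check, sitagliptin.** The guideline column starts dose reduction at 50 (half dose for 30 to 50). The reminder starts below 45. From 45 to 50 the guideline column asks for a reduction and the reminder gives none. Below 45 both columns ask for a reduction.

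**The case against.** The strongest reply is that the two columns do different jobs. One reports a source and the other is the trial's adaptation of it, in a CDSS that Section 3.2.1 says a multidisciplinary team will design. The columns also part openly elsewhere: glyburide and gliquidone have different cut-offs, and miglitol has a reminder where the guideline cell holds only a slash. This stands. A reader might infer that Table 4 contradicts itself, with two opposed instructions in force at once. The document does not support that: the natural reading is one adopted rule that departs, unexplained, from the source beside it.

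The second reply is that the error, if there is one, may lie in the guideline cell. That also stands. The guideline is not at hand, so the reminder could be right and the guideline cell miscopied. It would go too far to say that the CDSS is shown to recommend a contraindicated drug.

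The third reply is that the consequence is small. The CDSS is described as giving "non-intrusive, real-time clinical decision support during patient encounters"; patients at eGFR 15 to 24 are in stage 4 and so trigger the nephrology referral prompt in item 5(1); acarbose enters no outcome; and a prompt to reduce is not shown to be worse than no prompt in control centres. All of this limits the harm. It does not explain the cell, and a referral prompt does not correct dosing text shown at the same visit.

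A reader might also fault the sitagliptin reminder for giving no dose size. Unsized reminders are usual in that column, saxagliptin's among them, so that is a matter of preference. Only the gap between 45 and 50 is worth checking. Nor does the acarbose cell show that the consent waiver was unsound: Section 3.4.6 gives several grounds and does not name this guideline.

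**Conclusion.** The point holds as an unexplained relaxation in one cell of a safety table. The mismatch itself is certain: both cells are legible, share a cut-off, and no text accounts for the difference. It is the only one of six readable rows in which a stated contraindication is weakened, which suggests a slip more than a policy but does not prove one.

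Its size is modest. It concerns acarbose users with eGFR from 15 up to 25 in intervention centres, a number the protocol does not give. Any harm depends on two assumptions: that the guideline cell was copied correctly, and that the reminder column is what physicians see. Neither can be confirmed from the protocol. The sitagliptin threshold is a minor companion point. The sample size, power and planned analyses are untouched.

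**What to change.** 1. Check the acarbose cell against the cited guideline. If the guideline cell is correct, change the reminder to a contraindication below eGFR 25, or state in a table note why the trial departs from the guideline. If the guideline cell is a copying slip, correct that cell and leave the reminder.
2. Add one sentence to item 6(4) of Section 3.2.1 saying that the reminder column is what the CDSS displays.
3. At the same time, check whether the sitagliptin reminder should start at 50 instead of below 45.
4. Date any change to the CDSS rules. If the system is already live, notify the ethics committee. The protocol does not settle this: patient selection and ethics approval are described in the past tense, training and activation in the future.

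The cost is one acarbose cell or a note, possibly one sitagliptin cell, one sentence, and the matching rule edit in the 15 intervention centres. No patients, visits or analyses are added. The only real burden is a recorded version change, with an ethics notification if the CDSS is in use.
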